### Evidence-based intervention

The evidence-based intervention to be implemented into practice is brief physical activity counselling embedded in routine care by hospital-based physiotherapists. The intervention development has been led by LH with oversight from CG who has extensive expertise in developing behaviour change interventions. The intervention is based on current evidence of effective elements of physical activity counselling [2, 4] and is informed by the 5As model of brief counselling (Assess, Advise, Agree, Assist, Arrange) [1] and behavioural theory [37, 38], with the use of motivational interviewing techniques and culturally appropriate language to ensure person-centred care. Table 1 provides details of the components of the intervention using the TIDieR checklist [34]. Any adaptations to the counselling intervention throughout the trial will be documented using the Framework for Reporting Adaptations and Modifications to evidence-based interventions [39].

**Table 1 Tab1:** Evidence-based intervention description using the Template for Intervention Description and Replication (TIDieR) checklist

Brief name	Brief physical activity counselling within routine physiotherapy care
**Why**	Physical inactivity is a global health problem, with estimated 5.3 million deaths per year. Brief physical activity counselling (e.g. 5As model) [1] delivered by healthcare professionals as part of routine care is seen as opportunistic healthcare to address a public health problem. Evidence indicates that for every 12 sedentary people who receive physical activity counselling within healthcare at least one will increase activity to meet physical activity guidelines for health benefits [6]. As a public health intervention, this has the potential for community-based health benefits and healthcare cost savings. A theoretical basis combining Capability Opportunity Motivation-Behaviour change theory and Self Determination Theory informs intervention components and underpins patient materials.
**What procedures**	Patients receive their usual physiotherapy care to address the therapeutic reason that they have been referred for physiotherapy. Within this routine care, the physiotherapist will incorporate brief physical activity counselling comprising the following: ➢ Ask: Raise the topic of physical activity with permission (use motivational interviewing techniques and consider cultural influences throughout). ➢ Assess: Current physical activity level (objective and/or subjective); influences on physical activity using COM-B model. ➢ Advise: Discuss the benefits of physical activity; benefits of change; amount, type and intensity of physical activity (use elicit-provide-elicit framework). ➢ Agree: Collaboratively set 6–12-month behavioural sustainable goal(s); set short-term physical activity goals (use confidence scales for goal setting); develop action plan: what, where, when, how much, who with (include what if…. to anticipate barriers). ➢ Assist: Self-monitoring strategy (checklist, practice sheet, step count), assess/re-assess physical activity and goals, discuss barriers/facilitators, collaboratively identify community/home physical activity options, share plan for social support, build competence, control, connection (Self-Determination Theory). ➢ Arrange: Referral/contact/recommendation for healthcare/community/home-based physical activity, social support for practical (e.g. transport), emotional and motivational (e.g. family, friend, neighbour, carer, exercise/health professional)
**What materials**	Physiotherapists have access to a Microsoft Teams site that includes patient-facing resources: ➢ Handouts on physical activity guidelines and benefits of physical activity for a range of health conditions and produced by a number of organisations (e.g. Moving Medicine UK, Arthritis Association Australia, Australia National Disability Service Scheme, Cancer Council of Australia). Where available, handouts are available in English, Arabic and Vietnamese. ➢ Worksheets developed from a range of organisations (e.g. Agency for Clinical Innovation, National Institute on Aging) ➢ Study-developed worksheets including action plans, goal setting sheets, practice sheets, checklists, pedometer recording sheets, activity diary, Smartphone step counting instructions. ➢ Study-developed searchable activity directory with details of local physical activity opportunities that can be searched based on type of activity, cost, location. In addition, each team was provided with 10 pedometers (Yamax CW300) to use as they wished with patients.
**Who provided**	The intervention will be delivered by tertiary trained physiotherapists employed in the local health district who consent to participate in the study. Physiotherapists in the teams randomised to the immediate group, will receive the multi-faceted implementation strategy to support them to deliver physical activity counselling within routine care.
**How**	The physical activity counselling is delivered within routine care. How routine care is delivered may differ between teams and hospital sites but is most likely to be face-to-face (some virtual if COVID-19 restrictions apply). Any handouts, booklets or pedometers will be provided during the face-to-face session.
**Where**	Where the intervention is delivered may differ between teams and hospital sites but is likely to be delivered in an inpatient, outpatient or community setting within the boundaries of South Western Sydney Local Health District in the state of New South Wales, Australia.
**When and how much**	The frequency and duration of routine care will differ between services and sites and patient types. Data collected as part of pre-implementation work found that regardless of setting (inpatient, outpatient, mixed), physiotherapists reported an average of at least six occasions of service per patient lasting over 30 min per session [24]. Brief physical activity counselling is likely to be < 5min within these usual care sessions.
**Tailoring**	This is a tailored intervention. Depending on patient type, setting and frequency of interaction, the components of physical activity counselling will be incorporated. The core elements that all should receive include assess, advise and arrange using motivational interviewing techniques.

### Multi-faceted implementation strategy

The multi-faceted implementation strategy will be delivered by the research team to clinical physiotherapists randomised to the immediate-implementation group within their clinical teams (where possible) to support them to incorporate brief physical activity counselling into their routine practice. The primary implementation strategies will include education, training, tailored strategies to address community referral barriers, creation of a learning collaborative across the district, team facilitation, and audit and feedback to build clinicians’ Capabilities, Opportunities and Motivations to deliver brief physical activity counselling within routine care (see Table 2).

**Table 2 Tab2:** Description of multi-faceted implementation strategy delivered to teams of physiotherapists mapped to Behaviour Change Wheel [37]

Implementation strategy [40]^**a**^	Mode of delivery/where/length/who delivered	Time-frame	Proposed mechanism of action			Intervention content	
			Barriers targeted	COM-B domains [41]	COM-B intervention functions	BCTs	Detailed explanation
Education	Series of short (2–8 min) education videos /online/~ 45 min in total/ LH, BB, research physiotherapists, consumers	Prior to attending workshop 1	Knowledge of PA guidelines, benefits of PA, consequences of inactivity, % meeting guidelines, what is PA counselling, what is the evidence for PA counselling and “what works” for supporting behaviour change, how many people to treat to have an effect, how many physiotherapists currently do it and if they don’t what stops them (include local data), what do patients think	Capability Psychological-knowledge; Motivation-reflective & automatic	Education; persuasion	Information about health consequences; Feedback on behaviour; Feedback on the outcome(s) of the behaviour; Information about others’ approval; Credible source; Salience of consequences; Feedback on behaviour; Social comparison; Identification of self as a role model	Short videos on the study, what is PA, what are the PA guidelines, benefits of PA from a patient perspective, what is PA counselling, behaviour change theories, raising the topic of PA as PT, raising the topic of PA with CALD patients
Education and training (conduct educational meetings and ongoing training, make training dynamic, promote adaptability)	Workshops 1 & 2: face-to-face workshop/at team’s hospital/maximum 4 h/LH	Workshop 1: 2–3 weeks after hospital rotation Workshop 2: 3 months later	How to do the different elements of PA counselling within usual care (Ask, Assess, Advise, Agree, Assist, Arrange, incorporating motivational interviewing techniques and behaviour change theories); skills at initiation & negotiating discussions about PA; prioritizing within usual care session; forgetting to ask or document about PA; lack of resources to do PA counselling; PA counselling not usual practice in clinical teams; building motivation in patients	Capability Psychological-cognition, interpersonal & self-regulation; Motivation-reflective & automatic; Opportunities-physical & social	Education; training; enablement; persuasion; modelling; environmental restructuring	Instruction on how to perform a behaviour; demonstration of the behaviour; feedback on the behaviour; behavioural practice/rehearsal; social support (practical); goal setting (behaviour); action planning; information about others’ approval; social comparison; identification of self as a role model; prompts/cues; adding objects to the environment; Problem-solving	Made up of presentations (live & pre-recorded) from PTs, behavioural expert, CALD expert, patients (e.g. how to do the different elements of PA counselling and resources to support this); tasks (e.g. role-playing, using scripts, reviewing resources), discussions (e.g. group sharing reflections & experiences of the content presented and practised). Paper manual with slides and resources given to each participant); link to online resources including https://movingmedicine.ac.uk/
Create a learning collaborative	Communication platform/online-Microsoft Teams/length project/MJ, LH	Added at workshop 1	Lack of resources to set action plans, find local opportunities, measure PA, PA counselling not usual practice in clinical teams, promoting PA counselling not seen as a priority across the district, lack of time to find resources	Opportunity-social & physical; Motivation-reflective	Training; enablement; modelling; persuasion	Adding objects to the environment; social support (practical); problem-solving; action planning; social support (emotional); feedback on the behaviour	Access to online videos and workshop presentations, sharing resources developed across teams, place to communicate, ask questions, share feedback on audit
Tailored strategies to address community referral barriers (capture and share local knowledge)	Not yet determined, may vary between teams/LH, the research team	Start at workshop 1	How to find PA opportunities in the local community, how to refer to local community PA opportunities	Capability Psychological-cognition & knowledge; Motivation-automatic; Opportunity-physical & social	Environmental restructuring; enablement; modelling; training	Adding objects to the environment; social support (practical); problem-solving; demonstration of the behaviour; instruction on how to perform a behaviour	Provide training in finding PA opportunities, help to develop links, referral resources, evaluation tools of community PA opportunities
Facilitation^b^ (change record systems, promote adaptability, capture and share local knowledge) and Audit & Feedback within teams	Mix face-to-face & remote/in their clinical settings/monthly (1–2h)/LH	Between workshops 1 and 2	Fitting PA in usual sessions including measuring PA; lack of suitable PA resources (for physiotherapist & patient); how to find PA opportunities in the local community; how to refer to local community PA opportunities; PA counselling not usual practice in clinical teams	Opportunity-physical & social; Capability-knowledge & cognition; Motivation-reflective & automatic	Education; training; enablement; modelling; environmental restructuring	Demonstration of the behaviour; social support (practical); self-monitoring of behaviour; problem-solving; action planning; social support (emotional); feedback on the behaviour; behavioural practice/rehearsal; prompts/cues; adding objects to the environment	Working with the team to identify/modify/develop resources for their team (including local activity directory or similar resource), identify & connect with appropriate PA opportunities, modify physiotherapy assessment forms to include PA information to collect, audit and feedback with a colleague between workshops.

Key: *PA* Physical activity, *CALD* Culturally And Linguistically Diverse, *PT* Physiotherapist, *BCTs* Behaviour Change Techniques

^a^Secondary implementation strategies are in brackets; ^b^Facilitation: “A process of interactive problem solving and support that occurs in a context of a recognized need for improvement and a supportive interpersonal relationship” p.9 [40]

The development and delivery of the multi-faceted implementation strategy is led by LH (with input from CG and BB for the education and training aspects) who has a 17-year experience as a clinical physiotherapist, has had training in behaviour change methodology, implementation science and motivational interviewing, and holds an honorary position in the local health district. The Consolidated Framework for Implementation Research (CFIR) [42] has been used as an overarching framework to guide the multi-faceted implementation strategy development (see Supplemental file 1). The implementation strategies were derived from the Expert Recommendations for Implementing Change (ERIC) project [40] and the Behaviour Change Wheel [37] and are informed by literature describing barriers that physiotherapists report stop them from incorporating brief physical activity counselling into routine practice [25–28] as well as local barriers identified during informal consultations and a formal survey with clinical physiotherapists in the district as part of pre-implementation work [24]. Any adaptations to the implementation strategies will be documented throughout the trial using the Framework for Reporting Adaptations and Modifications to implementation strategies [43].

### Data collection methods and outcome measures

As a hybrid type II study [29], patient-level effectiveness and implementation outcomes will be measured. All effectiveness outcomes (excluding device-measured physical activity and impressions of physiotherapy) as well as demographic information and co-morbidities will be assessed at baseline to enable a description of the patient-participant’s baseline characteristics and to obtain values to enter as covariates in the models comparing groups at follow-up. At the time of consent, the treating physiotherapist will provide the participant with a copy of the paper-based survey. This will be completed independently by participants or assisted by study staff over the telephone who are blinded to physiotherapy team allocation. At 6 months post-baseline, follow-up paper-based surveys will be mailed to participants and followed up by blinded research staff if surveys are not returned by mail.

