##### Healthcare utilisation

This will be collected within New South Wales Health directly from the Activity-Based Management portal. The frequency of all health encounters captured by this system (i.e., hospitalisations, emergency department presentations and non-admitted activities such as specialist consultation and physiotherapy) that participants from both groups have during the 6-month trial period will be collected and costed using routine sources including DRG-based costs from the National Hospital Cost Data Collection [51] for inpatient presentations and Medical Benefits Schedule (MBS) and Pharmaceutical Benefits Schedule (PBS) for outpatient utilisation to inform the trial-based economic evaluation.

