##### Patient-level effectiveness outcomes

The primary analysis will evaluate the effect of the multi-faceted implementation strategy to train, support and facilitate physiotherapists to deliver brief physical activity counselling as part of their routine care [targeted at the cluster level] on primary and secondary effectiveness outcomes. The main (intention-to-treat (ITT)) dataset analysed will be constituted of all patients recruited into the study irrespective of what amount of physical activity counselling they received from their treating physiotherapist. For the continuous outcomes, multiple linear regression will be used with a group (immediate-implementation vs. waitlist control) as the primary independent variable and baseline scores as a covariate. Binary logistic regression will be used to compare groups on dichotomous outcome measures with the group as the primary independent variable.

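### Healthcare utilisation is listed as a secondary effectiveness outcome but is collected only during follow-up, so the baseline covariate the plan implies for it is not provided

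*Protocol article*

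**What the plan says.** Four places in the protocol article bear on this.

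- **Data collection methods and outcome measures** sets a general rule: "All effectiveness outcomes (excluding device-measured physical activity and impressions of physiotherapy) as well as demographic information and co-morbidities will be assessed at baseline". One stated purpose is "to obtain values to enter as covariates in the models comparing groups at follow-up". Two exceptions are named, and healthcare utilisation is neither of them.
- **Healthcare utilisation**, placed under Secondary effectiveness outcomes, names an administrative source: "This will be collected within New South Wales Health directly from the Activity-Based Management portal". The window is the encounters "that participants from both groups have during the 6-month trial period will be collected and costed using routine sources", and the stated use is "to inform the trial-based economic evaluation". No period before baseline is mentioned.
- **Patient-level effectiveness outcomes** covers the primary and secondary effectiveness outcomes. For continuous ones it specifies linear regression on group, with "baseline scores as a covariate".
- **Economic analysis** compares average cost and average outcome by arm, bootstraps the result, and ends its horizon with the trial. It mentions neither a baseline cost nor a baseline-adjusted cost model.

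**The concern.** Read together, the baseline rule and the regression specification imply a baseline covariate for every continuous effectiveness outcome outside the two exceptions. Healthcare utilisation is outside them, and its collection window supplies no such value. An analyst following the article would find the covariate missing for this one outcome and would have to decide later what to do.

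What is at stake is precision and protection against imbalance in a secondary outcome and in the costs built from it. The teams range from inpatient rehabilitation to musculoskeletal outpatients, and the patients from osteoarthritis to stroke and amputation, so prior health service use is likely to vary widely. Minimisation uses only the team's volume of occasions of service. Patients are enrolled by the treating physiotherapists, and the plan describes staff who help with the baseline survey as blinded to team allocation, which implies that teams are already allocated by then. Case mix can therefore differ between arms both by chance and through who is enrolled. A measure of prior use would show such a difference and allow adjustment for it.

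**Working it through.** **Does a baseline value exist for utilisation under the plan?**

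1. Rule: all effectiveness outcomes have a baseline value, except accelerometer-measured activity and patients' impressions of their physiotherapy.
2. Is utilisation an effectiveness outcome? By its heading, yes.
3. Is it excepted? No. The impressions exception matches the separate Healthcare evaluation questionnaire, not the portal data.
4. Could the baseline survey supply it? The baseline instrument is the paper form: "At the time of consent, the treating physiotherapist will provide the participant with a copy of the paper-based survey". Utilisation has a different named source, the portal, and a window that covers only the trial period.
5. Result: no baseline value is provided, so the baseline rule, the collection window and the regression specification do not agree for this outcome.

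**Are the costs affected in the same way?** No. The economic section compares arm averages over the trial, and the 6-month window fits that horizon. Nothing promised there is missing.

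**Is the sample size affected?** No; utilisation is not an input. For completeness, the stated figure reproduces. With a difference of 1.5 h/week, SD 4.4, alpha 0.025 (taken as two-sided) and 80% power, 164 per arm are needed before clustering. The design effect is 1 + (10 − 1) × 0.05 = 1.45. Reading the stated 0.6 as a baseline to follow-up correlation, the adjustment factor is 1 − 0.6² = 0.64. Then 164 × 1.45 × 0.64 = 152.2 per arm, about 304 in total against the stated 300.

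**What might a baseline count be worth?** The correlation *r* between prior and later 6-month use is not in the document, so a range is assumed. The residual variance fraction is 1 − r², and the interval width ratio is its square root.

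| Assumed r | 1 − r² | Width ratio | Narrower by |
|---|---|---|---|
| 0.30 | 0.91 | 0.95 | 5% |
| 0.45 | 0.80 | 0.89 | 11% |
| 0.60 | 0.64 | 0.80 | 20% |

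These are individual-level figures for a linear relation. They ignore clustering and the skew usual in encounter counts and costs.

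**How plausible is a chance imbalance in setting?** As an illustration, assume 15 of the 30 teams are inpatient teams and that setting is unrelated to the minimisation factor; neither is stated. The chance that an arm of 15 holds 7 or 8 inpatient teams is 2 × C(15,7) × C(15,8) / C(30,15) = 2 × 6435² / 155,117,520 = 0.53. In the remaining 47% the split is at least 9 against 6, a gap of 20 percentage points or more in the share of inpatient teams.

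**The case against.** The best case for the plan is that utilisation is in substance a costing input. Its stated purpose is the economic evaluation, the secondary research question on patient outcomes does not list it, and no utilisation regression is named. The baseline sentence is followed at once by the paper survey, so it can be read as covering the questionnaire measures only. All of this is fair. It makes the mismatch smaller, but the heading and the explicit list of exceptions still bring utilisation under the rule.

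A reader might also infer three stronger things that the document does not support:

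- *That the cost comparison lacks a pre-trial value the plan promised.* The economic section makes no such promise, and the handling of baseline costs is commonly left to a fuller analysis plan.
- *That utilisation cannot be analysed.* A model with group alone remains available. Step count is already a continuous secondary outcome that is openly exempt from baseline measurement.
- *That the baseline value is lost.* The planned source is an administrative portal, and a longer look-back may well be obtainable from it.

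It can also be said that randomisation makes the unadjusted comparison unbiased and that chance imbalance is reflected in the interval. That holds for the allocation of teams. It answers the concern only in part here, because the treating physiotherapists enrol the patients, apparently after their team has been allocated.

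**Conclusion.** The point holds as an internal inconsistency with a cheap improvement attached. The article implies a baseline covariate for utilisation and does not provide for collecting one. It does not touch the co-primary outcomes or the sample size. For the incremental cost, baseline adjustment would strengthen the analysis, but its absence breaks no commitment.

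The possible gain, intervals about 5% to 20% narrower, rests wholly on an assumed correlation of 0.3 to 0.6 and on individual-level reasoning. With clustered, skewed data, and with inpatients whose look-back may include part of the index admission, the true gain could lie outside that range. The illustration of imbalance between teams likewise rests on an assumed even split of inpatient and outpatient teams.

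**What to change.** In the Healthcare utilisation section, extend the planned portal extract to the same encounter types for the 6 months before each patient's baseline date. Use that count as the baseline covariate in any between-group comparison of utilisation, and its cost as the covariate in a baseline-adjusted estimate of incremental cost.

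State how the look-back treats an index admission that began before baseline. State also how it treats physiotherapy contacts between the start of care and consent, since patients are invited at one session and consented at the next. Contacts after the team's allocation are not clean baseline information.

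If pre-baseline records cannot be accessed, add healthcare utilisation to the exceptions in the Data collection section, and say that it will be compared without a baseline covariate. That removes the contradiction but gives up the precision and the check on case mix.

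The cost is a longer extract from a source already in use and possibly a line of consent or ethics wording to cover earlier records. No extra patients or visits are needed.
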